**Methods:**

We are leveraging 3D reconstruction and semantic segmentation techniques to create a digital twin of the campus that houses Mahidol University’s disability college. We will do cross-over randomization, and two groups of randomized VI students will deploy this augmented platform in two phases: a passive phase, during which the wearable will only record location, and an active phase, in which end users receive orientation cueing during location recording. A group will perform the active phase first, then the passive, and the other group will experiment reciprocally. We will assess for acceptability, appropriateness, and feasibility, focusing on experiences with VIS^4^ION. In addition, we will test another cohort of students for navigational, health, and well-being improvements, comparing weeks 1 to 4. We will also conduct a process evaluation according to the Saunders Framework. Finally, we will extend our computer vision and digital twinning technique to a 12-block spatial grid in Bangkok, providing aid in a more complex environment.

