### Explanation for choice of comparators {6b}

This study aims to test the hypothesis that VIS^4^ION is a wearable assistive technology that assists spatial cognition in VI populations, enhancing personal freedom and independence, health, and well-being. VIS^4^ION is able to take advantage of contemporary, state-of-the-art technologies and approaches. The backpack embodiment was a careful decision made with end users to enhance acceptance; user-centric design approaches will be used for the entirety of the project.

There is a clear lack of comparison of the effect of wearable assistive technology on health and quality of life, including independent and social engagement in active and passive mode; trials evaluating the effectiveness of assistive technology rarely included mobility metrics, subjective and objective assessments of the quality of life, acceptability and appropriateness as comparators. Therefore, we will have comprehensive metrics to evaluate the outcomes in the first week and fourth week of extended use of wearables in passive and active phases. In “the passive phase,” the wearable will be maintained in a monitoring mode and simply acquire data, providing no assistance/feedback on location and orientation. During the active phase, the wearable will have an activated assistive mode, i.e., the wearable will acquire data and simultaneously provide assistance/audio feedback.

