Each FGD session will last roughly 60 min and include participants’ perceptions and experiences while navigating the VIS^4^ION system. The FGDs will be guided by pre-determined questions related to general perceptions of the VIS^4^ION system, as well as thoughts on the facilitators and barriers of the intervention. The FGD sessions will be audio-recorded verbatim and later transcribed and translated into English by the research team. During the sessions, the research team member will also take field notes.

#### Aim 4

A cohort of 20 (new) participants will be recruited to assess extended-use benefits over one month. We will create two groups for the randomized crossover design. Each participant will be randomized to either sequence A (10 participants) or sequence B (10 participants). During the first 15 days, group A will go through an active phase and then a passive phase for the next 15 days. Reciprocally, group B will go through a passive phase for the first 15 days and then an active phase for the second half of the month. During the passive phase, the wearable will be maintained in a monitoring mode and simply acquire data, providing no assistance/feedback on location and orientation. During the active phase, the wearable will have an activated assistive mode, i.e., the wearable will acquire data and simultaneously provide assistance/audio feedback. We will evaluate the effectiveness of the wearable for increasing navigation and quality of life. We hypothesize that the VIS^4^ION wearable will improve navigation and quality of life in individuals with visual disabilities.

During the active phase, subjects will complete their daily activities while wearing VIS^4^ION and using the mapping and localization microservice to facilitate wayfinding. Throughout the study we will monitor navigation performance through the same metrics as delineated in Aim 2 [week 2 compared to week 4], as well as to monitor for any falls that may occur (IMU-based alerting); we will also subjectively assess visual function through the 25-Item National Eye Institute Visual Function Questionnaire (VFQ25) [29], physical function and mobility, through the International Physical Activity Questionnaire (IPAQ) [30, 31], and QoL, through the World Health Organization QoL Brief (WHO-QoL-BREF) [32, 33]. The subjective assessments will be performed on day 0 (day of device delivery and initiation) and on the final day of the trial (day 31).

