We will perform a content analysis of the transcripts and notes using NVIVO software [36]. Specific quotations, group interactions, and observations will be assigned codes based on content. The following are the core acceptability and appropriateness outcomes that will be assessed: (a) satisfaction or agreeability with the refined intervention design; (b) perceptions on how the intervention can be adopted within their setting; (c) perceived willingness or interest to participate; and d) perceived relevance and fit of the intervention for the setting. Significant inductive (emerging) codes will also be identified, assessing for differences by sex. Coded items will be grouped into a hierarchical, branching structure in which broad concepts are first identified. The themes and interpretive ideas emerging from those constructs are labeled using constant comparison techniques and subsequently synthesized using matrices structured by the main themes of the analysis [39, 40]. In addition, we will measure acceptability, feasibility, and appropriateness as lumped average scores (5-point Likert scale) across a 27-question post-interview questionnaire. Averages of > 2.5 will indicate an overall positive rating on each dimension, although low average scores on individual questions within each dimension (i.e., non-lumped) will be used to aid product development.

#### Aim 4

We will evaluate the effectiveness of our approach to increase efficient mobility among BLV students, as well as health and well-being. Descriptive statistics will be generated for quantitative data, and thematic content analysis will be performed for qualitative data. We will perform a content analysis of the transcripts and notes using NVIVO software [36], in a manner similar to what has been described above in Aim 3. Results will be categorized according to the seven dimensions of the Saunders Framework: fidelity, dose delivered, dose received (exposure), dose received (satisfaction), recruitment, reach, and context. Formative data will be reported iteratively to the study team throughout the trial, in order to improve intervention delivery, while summary data will be reported at the end of the trial along with the results of the trial. We will compare pre/post-differences in subjective assessments and in navigation and health metrics.

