We will compare pre-post metrics using Bayesian model comparison techniques. For example, we will compare fall rates using an exponential waiting-time model of duration between falls (Poisson rate of falling,) based on the ratio (Fig. 5):

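### Aim 4 states calendar and pre/post comparisons for a randomised crossover; pooled as written, these estimate the period effect and the device effect drops out of the device-recorded outcomes

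*Protocol article*

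**What the plan says.** The Aim 4 text under Intervention description {11a} sets out a two-sequence crossover: "Each participant will be randomized to either sequence A (10 participants) or sequence B (10 participants". For the order of modes it says "During the first 15 days, group A will go through an active phase and then a passive phase for the next 15 days", while "group B will go through a passive phase for the first 15 days and then an active phase for the second half of the month". Trial design {8} says the same.

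The comparisons stated for this design are by calendar time or pre/post:

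- Intervention description {11a}, Aim 4: "we will monitor navigation performance through the same metrics as delineated in Aim 2 [week 2 compared to week 4" (the bracket closes there).
- Outcomes {12}, Aim 4 column: social time and fall rates are compared pre to post.
- Statistical methods {20a}, Aim 4: "We will compare pre/post-differences in subjective assessments and in navigation and health metrics", and "We will compare pre-post metrics using Bayesian model comparison techniques", with fall rates as the worked example.

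The questionnaires (VFQ25, IPAQ, WHO-QoL-BREF) are given on day 0 and day 31 only.

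The week labels differ elsewhere. The abstract says "we will test another cohort of students for navigational, health, and well-being improvements, comparing weeks 1 to 4". Explanation for choice of comparators {6b} speaks of "comprehensive metrics to evaluate the outcomes in the first week and fourth week of extended use of wearables", in passive and active phases. The abstract also attaches the crossover to the cohort assessed for acceptability. In the body, that cohort (Aims 2 and 3) has a fixed passive-then-active order, and the crossover belongs to the new Aim 4 cohort.

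**The concern.** The pre/post metrics come from Aim 2. There every participant wears the system in passive mode for the first five days and in active mode for the last five, so post minus pre is the same thing as active minus passive. In Aim 4 half the participants switch from on to off and half from off to on, and that equivalence is lost. A before/after contrast over the whole group then measures what changed between the first and second half of the month, whatever the mode.

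At stake is the only randomised comparison in the programme. An effective device could show no effect on paths, times, activity or falls. Conversely, learning the campus or a change in the term timetable could be credited to the device.

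**Working it through.** **Inputs.** From Intervention description {11a}: sequences A (active, passive) and B (passive, active), 10 participants each, 15 days per phase. From Sample size: 20 subjects, a 40% difference in path length, an SD of length ratios of at most 2.5, power of at least 0.8. The sample-size inputs are stated for the first phase; no separate Aim 4 calculation is given. The significance level and sidedness are not stated; 0.05 is assumed.

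**1. Where the weeks fall.** Week 2 is days 8–14, wholly in period 1. Week 4 is days 22–28, wholly in period 2. Week 1 (days 1–7) is also wholly in period 1, so comparing weeks 1 and 4 has the same structure.

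**2. What the stated contrast estimates.** Let τ be the device effect (active minus passive), π the period effect (period 2 minus period 1), and D a participant's week 4 value minus week 2 value.

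- Group A goes active to passive: E[D] = π − τ.
- Group B goes passive to active: E[D] = π + τ.
- Pooled: [10(π − τ) + 10(π + τ)] / 20 = π.

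The device effect drops out whatever its size and whatever the SD. If allocation drifted to 12:8, the pooled mean would be π + τ(8 − 12)/20 = π − 0.2τ, a small remnant of the wrong sign.

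**3. What a sequence-based contrast estimates.** (mean D in B − mean D in A)/2 = [(π + τ) − (π − τ)]/2 = τ. The period effect drops out instead.

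**4. Questionnaires, day 0 to day 31.** Let θ be the change over time without assistance. Group A ends passive, so its expected change is θ; group B ends active, so its change is θ + τ. Pooled: [10θ + 10(θ + τ)]/20 = θ + τ/2. This takes the score to reflect the mode at the end of the month. The effect is halved and mixed with time, but not cancelled. The same would hold for blood pressure and BMI if they are taken at those two times; Outcomes {12} says only pre to post.

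**5. The protocol's own power figure.** On the log-ratio scale |ln 0.6| = 0.511. Reading the SD as ln 2.5 = 0.916, the standardised effect is 0.511/0.916 = 0.557. With a one-sided normal approximation, 0.557 × √20 − 1.645 = 0.848, which gives power 0.802 and reproduces the stated 0.8. A two-sided t-test gives 0.658. If 2.5 is taken directly as the log-scale SD, the two-sided t-test gives 0.14.

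**6. Illustrative rejection rates.** 40,000 simulated crossovers, 10 per sequence, SD of D = ln 2.5, two-sided 0.05:

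| Device effect τ | Period effect π | Pooled week 4 − week 2: mean, rejects | Sequence-based contrast: mean, rejects |
|---|---|---|---|
| 0.511 | 0 | 0.00, 2.5% | 0.511, 66% |
| 0 | 0.3 | 0.30, 29% | 0.00, 4.9% |
| 0.511 | 0.3 | 0.30, 20% | 0.51, 65% |
| 0 | 0.511 | 0.51, 66% | 0.00, 4.9% |

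In the first row the pooled test rejects less often than 5% because the opposite shifts in A and B widen the spread of D around a mean of zero. The period effects are chosen for illustration; the documents give none.

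**The case against.** The strongest reply is that nothing in the text says the sequences are pooled. The bracket naming weeks 2 and 4 could mean the later week of each 15-day phase, to be compared within a person according to mode. The comparators section does mention passive and active phases, Aim 4 is called a randomised crossover, and period and sequence terms are commonly left to an analysis plan, which is not shown. This reading is possible. But no Aim 4 statistical text states it: every comparison named there is by calendar week or pre/post, and none is active versus passive. An analysis plan that followed the protocol would inherit the fault, and one that did not would contradict it.

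A second reply is that Trial design {8} calls Aim 4 exploratory, and the recorded data can be re-analysed by mode. Both are true. Yet the Objectives call for an extended-use randomised controlled trial, and Aim 4 carries a stated hypothesis of improvement.

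Three stronger readings are not supported:

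- A reader might infer that the effect cancels for every Aim 4 outcome. For the day 0/day 31 questionnaires it is halved and confounded with time.
- A reader might infer that carryover is ignored. The article describes no washout, but handling of carryover is commonly left to the full protocol or analysis plan, so its absence here is no finding.
- A reader might take the percentages as the trial's operating characteristics. They borrow a first-phase effect size and an assumed SD, and they use t-tests where the protocol plans a Bayesian model comparison. Also, Sample size describes the initial paths as shorter than those with the aid, while the simulation uses only the absolute size of that difference; the rejection rates do not depend on the sign.

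**Conclusion.** The point holds for the contrast as written. For path length, traversal time, social time, activity and falls, a week 2 versus week 4 or pre/post comparison pooled over two equal sequences estimates the period effect alone. This rests on two things only: the 10:10 allocation and pooling over sequences, which is the literal reading. It does not depend on the SD, the effect size or the choice of test, so it applies in expectation to the Bayesian fall-rate comparison too. The roughly 3% against 66% is an illustration of scale, conditional on ln 2.5 as the log-scale SD; with 2.5 as the log-scale SD the 66% would fall to about 14%.

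For the questionnaires the pooled change carries about half the device effect plus any time trend, and should not be read as a device effect.

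The week labels and the abstract's placement of the crossover contradict the body. The abstract's phrase about weeks 1 to 4 might denote a span rather than a contrast, but the comparators section names the first and fourth weeks, so the labels still need reconciling.

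**What to change.** - **Device-recorded outcomes.** In Intervention description {11a}, Outcomes {12} and Statistical methods {20a}, define the Aim 4 contrast for path length, traversal time, social time and activity as within-participant active minus passive, over matched windows of each phase (for example weeks 2 and 4, labelled by mode), with a period term.
- **Falls.** Define the contrast in the same way, and apply the planned Poisson model comparison to rates by mode instead of pre versus post.
- **Questionnaires.** Compare group B with group A at day 31, adjusted for day 0. State that this contrasts ending active with ending passive, because no assessment at the switch is described. Do not present the pooled pre/post change as a device effect.
- **Consistency.** Use one definition of the weeks in the abstract, the comparators section and Aim 4, and align the abstract's description of the cohorts with the body.

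**Cost.** For device-recorded outcomes the change is to wording only, since the wearable acquires data in both modes, plus one degree of freedom for period. The questionnaire comparison becomes a between-group one with 10 per group and is less precise. A within-person questionnaire contrast would need an added assessment at the switch, which is a change of procedure and not only of wording.

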### Trial design {8}

#### Phase 1

Aim 1: Create a “digital twin” of a particular campus (Ratchasuda — a disability college), testing both the performance of the service itself as well as the functional impact of the system.

Aim 2: Assess the ecology of VI students using the wearable, assessing the home range and activity level. A cohort of 20 VI students will use the wearable during navigation (1 week) in two phases: an initial passive phase, during which the wearable will only record location, and then an active phase, during which the location recording will be enhanced with orientation cueing.

Aim 3: Assess the acceptability, appropriateness, and feasibility of the wearable, as a navigation aid for the BLV, using the results of interviews and surveys to implement improvements to the system.

#### Phase 2

Aim 4: We designed an exploratory experiment to assess and monitor our participant’s health-related changes (increased mobility and QoL). This phase is planned as a prospective, randomized crossover, controlled, non-blinded study to compare to evaluate the effectiveness of the wearable for increasing navigation and quality of life. Twenty BLV participants will be randomized to group A (10 participants) and group B (10 participants). During the first 15 days, group A will go through an active phase and then a passive phase for the next 15 days. Reciprocally, group B will go through a passive phase for the first 15 days and then an active phase for the second half of the month.

Aim 5: We will test the generalizability of the new mapping service in a more challenging environment — testing system performance in Bangkok.

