**Table Tabb:** 

Aims	Aim 1	Aim 2	Aim 3	Aim 4	Aim 5
Tasks	1) Multiple correlation of actual to inferred 3D position (goodness of fit metric comparing the actual and inferred 3D positions) 2) Average error as a function of distance from the center of the 3D map (mapping precision will likely vary as a function of position within the mapped region). The precision metric compares performance consistency to the ideal) 3) Positioning (xy) accuracy and viewing angle accuracy (comparing actual performance to the ideal, i.e., accuracy, shows the size and direction of biases in performance) 4) Beta localization	1) Average changes in normalized path length and variability in path length (i.e., percent change in path length and path variance; comparisons of pre/post path length indicate a potential change in confidence and ability in following a path without getting lost) 2) Average changes in normalized traversal time (i.e., percent change in time; comparison of pre/post traversal times indicates potentially improved general mobility and navigation) 3) For destinations that denote social activities, compute mean difference in time spent on such activities pre to post (comparisons between pre/post means indicate potential changes in levels of social interaction) 4) Pre vs. post fall rates (a comparison to determine if fall rates increase/decrease) 5) Assess QoL using the VFQ25 and WHO-QOLBREF 6) Assess physical function and mobility using IPAQ	Measure acceptability, feasibility, and appropriateness as lumped average scores (5-point Likert scale) across post-interview questionnaire and focus-group discussions	1) Average changes in normalized path length (i.e., percent change in path length) 2) Average changes in normalized traversal time (i.e., percent change in time) 3) For destinations that denote social activities, compute mean difference in time spent on such activities pre-to-post 4) Measure overall activity using total path length/day and total travel time/day 5) Measure BP and BMI pre-topost, and correlate with measures 1–4 6) Pre vs. post fall rates 7) Assess QoL using the VFQ25 and WHO-QOLBREF 8) Assess physical function and mobility using IPAQ 9) We will also conduct a process evaluation according to the Saunders Framework	1) Multiple correlation of actual to inferred 3D position (goodness of fit metric) 2) Average error as a function of distance from the center of the 3D map (mapping precision will likely vary as a function of position within the mapped region) 3) Compare (*t*-test) correlations and (linear model) average error functions between Aims 1 and 5 to show generalizability

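### Aim 4 schedules its three questionnaires only on day 0 and day 31, so the crossover gives no within-person active-versus-passive comparison of VFQ25, IPAQ or WHO-QoL-BREF

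*Protocol article*

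**What the plan says.** Under Intervention description {11a}, Aim 4, the design is a two-sequence crossover: "Each participant will be randomized to either sequence A (10 participants) or sequence B (10 participants"). Sequence A: "During the first 15 days, group A will go through an active phase and then a passive phase for the next 15 days". Sequence B: "group B will go through a passive phase for the first 15 days and then an active phase for the second half" of the month. Passive mode records only; active mode records and gives feedback. The stated hypothesis is that the wearable improves both navigation and quality of life, and Trial design {8} describes the phase as evaluating effectiveness on both.

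The same Aim 4 text gives the questionnaire dates: "subjective assessments will be performed on day 0 (day of device delivery and initiation) and on the final day of the trial", day 31. No questionnaire is scheduled at the end of the first phase. Navigation, by contrast, is monitored throughout and compared between week 2 and week 4, one week in each mode.

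Statistical methods {20a}, Aim 4, plans: "We will compare pre/post-differences in subjective assessments and in navigation and health metrics". The text that follows says pre-post metrics will be compared by Bayesian model comparison.

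Two other places describe timing in general terms. The abstract speaks of comparing weeks 1 to 4. Explanation for choice of comparators {6b} speaks of outcomes in the first and fourth weeks, in passive and active phases.

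**The concern.** A crossover earns its efficiency by measuring each person under both conditions. Here the patient-reported outcomes are measured once before either condition and once after both. The change from day 0 to day 31 then contains active exposure, passive exposure and a month of time in every participant. An improvement could reflect the device, the novelty of wearing it, attention from staff, familiarity with the questionnaire, or the point reached in the academic term.

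The quality-of-life half of the Aim 4 hypothesis rests on these instruments. The gap is in data collection, so no later analysis plan can supply the missing scores.

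**Working it through.** **The plan's own figure.** The only power statement (Sample size) concerns first-phase path length with 20 subjects. With log ratio ln(1/0.6) = 0.511, log SD ln(2.5) = 0.916 and an assumed one-sided alpha of 0.05, power = Φ(0.511/(0.916/√20) − 1.645) = 0.802, which matches the stated 0.8. A two-sided test gives 0.703. Neither figure bears on the questionnaires, for which the protocol gives no figure.

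**Inputs from the protocol.** 20 participants, 10 per sequence; A is active then passive, B is passive then active; questionnaires on day 0 and day 31.

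**Notation.** δ is the effect of active mode while it is on. λ is the part of it still present at the end of a following passive phase (carryover). π₁ and π₂ are changes due to time alone at the end of phases 1 and 2.

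**1. What the present schedule estimates (expected change, day 31 minus day 0)**
- Sequence A: π₂ + λ
- Sequence B: π₂ + δ
- Average over both sequences: π₂ + (δ + λ)/2
- B minus A: δ − λ

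| Case | Average change | B minus A |
|---|---|---|
| Benefit only while active (λ = 0) | π₂ + δ/2 | δ |
| Benefit persists in full (λ = δ) | π₂ + δ | 0 |

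The average change cannot be separated from π₂ in either row. The between-sequence difference removes π₂ but vanishes if the benefit persists. A linear model with subject, visit, mode and carryover terms has rank 22 for 23 columns under this schedule, so δ is not estimable once carryover is allowed.

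**2. What an end-of-phase-1 questionnaire adds**
- Active minus passive, A: δ − λ + π₁ − π₂
- Active minus passive, B: δ + π₂ − π₁
- Mean of the two: δ − λ/2
- A minus B at the end of phase 1, as change from day 0: δ, free of carryover

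The model with carryover now has rank 24 for 24 columns, so δ and λ can be separated.

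**3. Precision, assuming λ = 0.** Assume also equal variance σ² and a common correlation ρ between visits; the protocol gives neither, so a range of ρ is shown.
- Day-31 difference between sequences, adjusted for day 0: (1/10 + 1/10)(1 − ρ²)σ² = 0.2(1 − ρ²)σ²
- Within-person contrast, 20 participants: 2(1 − ρ)σ²/20 = 0.1(1 − ρ)σ²
- Ratio: 2(1 + ρ)

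| ρ | Between sequences (σ²) | Within person (σ²) | Ratio |
|---|---|---|---|
| 0.5 | 0.150 | 0.050 | 3.0 |
| 0.7 | 0.102 | 0.030 | 3.4 |
| 0.8 | 0.072 | 0.020 | 3.6 |

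For an assumed effect of 0.5 SD and a two-sided 0.05 test, power at ρ = 0.5, 0.7 and 0.8 is 0.23, 0.32 and 0.42 between sequences, against 0.56, 0.78 and 0.92 within person.

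**4. If carryover is modelled.** With σ_w² = (1 − ρ)σ², the variance of δ under the three-visit schedule is 0.40σ_w². That equals the variance of the unadjusted between-sequence comparison of change scores available now: 2(1 − ρ)σ² × (1/10 + 1/10) = 0.40σ_w². The precision gain in step 3 therefore depends on carryover being negligible. What remains without that condition is that the mode effect becomes estimable separately from carryover.

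**The case against.** The strongest defence is that Aim 4 is labelled exploratory, that its purpose includes benefit over a month of use, that no quality-of-life outcome is named as primary, and that comparing changes between sequences is compatible with the text. This has some force. Several stronger statements that a reader might infer are not supported:

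- *The randomisation contributes nothing to Aim 4.* Navigation is compared between weeks in opposite modes with randomised order. For the questionnaires, the protocol does not say that the sequences are pooled, and an analysis plan could specify a between-sequence contrast.
- *Quality of life cannot be tested at all.* The day-31 contrast between sequences remains. It is weak and estimates δ − λ, but it is randomised.
- *The effect on activity is lost.* Only IPAQ self-report is affected. The Outcomes table lists device-recorded path length and travel time per day, available in both modes.
- *Blood pressure and BMI share the fault.* The table says only "Measure BP and BMI pre-topost". No dates are given, and in Aim 2 the same pre/post language means passive days against active days.
- *The within-person contrast is free of carryover.* No washout is described, and that contrast is biased by λ/2, although the present between-sequence contrast is biased by the full λ.

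One could also say that the week 1 and week 4 wording covers the gap. It is general, it does not place a questionnaire at the end of the first phase, and it does not match the only dates given for these instruments.

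The schedule itself survives all of this. Even an exploratory crossover needs a score in each phase to compare the modes within person, and Trial design {8} says the phase is to evaluate effectiveness on quality of life.

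**Conclusion.** The concern holds for VFQ25, IPAQ and WHO-QoL-BREF. With questionnaires on day 0 and day 31 only, the active-versus-passive effect on them cannot be estimated within person. A pre/post difference across both sequences would mix that effect, halved or whole, with time and novelty.

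The randomised contrast that survives has 2(1 + ρ) times the variance of the within-person contrast, 3.0 to 3.6 times for ρ of 0.5 to 0.8. This rests on assumed correlations, equal variances and no carryover. That the within-person pair is missing rests on none of these; it follows from the visit dates alone. Navigation and device-recorded activity are outside the finding. Blood pressure and BMI timing is unspecified rather than shown to be wrong.

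**What to change.** 1. Add VFQ25, IPAQ and WHO-QoL-BREF at the end of the first phase, before the mode is switched, keeping day 0 and day 31.
2. Analyse end-of-active minus end-of-passive within person with a period term. Use day 0 for adjustment and to examine carryover, and report the carryover-free phase-1 comparison between sequences alongside.
3. If a third assessment is not possible, specify the day-31 difference between sequences adjusted for day 0 as the analysis of these questionnaires. State that it assumes no carryover, and limit the quality-of-life claim accordingly.
4. Reconcile the week 1 and week 4 wording in the abstract and in section {6b} with the dates in the Aim 4 text.
5. State when blood pressure and BMI are measured. If they are to inform the mode comparison, put them on the same three-visit schedule.

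The cost is one extra questionnaire session for 20 participants and a little added burden. The protocol describes no contact at the switch, so the session may have to be arranged. Trial status says enrolment had not begun, so on the document's own dates the change could be made before any data were collected.
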